## Abstract

**Background:**

Cardiovascular diseases (CVDs) pose a significant global health challenge, necessitating innovative approaches for primary prevention. Personalized prevention, based on genetic risk scores (PRS) and digital technologies, holds promise in revolutionizing CVD preventive strategies. However, the clinical efficacy of these interventions requires further investigation. This study presents the protocol of the INNOPREV randomized controlled trial, aiming to evaluate the clinical efficacy of PRS and digital technologies in personalized cardiovascular disease prevention.

**Methods:**

The INNOPREV trial is a four-arm RCT conducted in Italy. A total of 1,020 participants, aged 40–69 with high 10-year CVD risk based on SCORE 2 charts, will be randomly assigned to traditional CVD risk assessment, genetic testing (CVD PRS), digital intervention (app and smart band), or a combination of genetic testing and digital intervention. The primary objective is to evaluate the efficacy of providing CVD PRS information, measured at baseline, either alone or in combination with the use of an app and a smart band, on two endpoints: changes in lifestyle patterns, and modification in CVD risk profiles. Participants will undergo a comprehensive assessment and cardiovascular evaluation at baseline, with follow-up visits at one, five, and 12 months. Lifestyle changes and CVD risk profiles will be assessed at different time points beyond the initial assessment, using the Life's Essential 8 and SCORE 2, respectively. Blood samples will be collected at baseline and at study completion to evaluate changes in lipid profiles. The analysis will employ adjusted mixed-effect models for repeated measures to assess significant differences in the data collected over time. Additionally, potential moderators and mediators will be examined to understand the underlying mechanisms of behavior change.

**Discussion:**

As the largest trial in this context, the INNOPREV trial will contribute to the advancement of personalized cardiovascular disease prevention, with the potential to positively impact public health and reduce the burden of CVDs on healthcare systems. By systematically examining the clinical efficacy of PRS and digital interventions, this trial aims to provide valuable evidence to guide future preventive strategies and enhance population health outcomes.

## Background

Cardiovascular diseases (CVDs) continue to pose a significant global health challenge, representing the leading cause of morbidity and mortality worldwide (1). With their multifactorial nature, CVDs encompass a range of conditions such as coronary artery disease, stroke, and heart failure, affecting millions of individuals and placing an immense burden on healthcare systems (2, 3).

The burden of CVDs is driven by various risk factors, including unhealthy lifestyles, genetic predisposition, and socioeconomic factors. Despite advancements in medical interventions and improved awareness of preventive measures, the incidence and prevalence of CVDs remain substantial, underscoring the need for innovative approaches in primary prevention (1–3).

Personalized prevention, tailored to an individual's unique genetic makeup and lifestyle characteristics, holds great promise in revolutionizing preventive strategies for CVDs. Among the emerging tools in this field, polygenic risk scores (PRS) have gained attention as a potential means of assessing an individual's genetic susceptibility to CVDs. By aggregating information from multiple genetic variants, PRS offers a comprehensive assessment of an individual's genetic risk profile, aiding in the identification of high-risk individuals who may benefit from targeted preventive interventions (4–6).

Additionally, the rapid advancements in digital technologies have opened up new opportunities for personalized healthcare delivery and behavior modification. Ranging from wearable devices monitoring physical activity, dietary, and sleep habits to smartphone applications promoting healthy habits, digital tools provide innovative ways to engage individuals and support sustainable lifestyle changes (7–9).

Despite the increasing interest in utilizing PRS and digital technologies for personalized cardiovascular disease prevention, their clinical efficacy and real-world impact are still to be fully elucidated. Furthermore, the efficacy of communicating the PRS to the person relies on the assumption that receiving genetic feedback will motivate individuals to change their behaviors and reduce their risk of developing the disease. A comprehensive evaluation of these interventions through large-scale prospective studies is necessary to determine their utility, feasibility, and potential benefits in reducing CVD risk at the population level.

Therefore, this paper presents the rationale and design of a randomized controlled trial (RCT) that aims to evaluate the clinical efficacy of PRS and digital technologies in personalized CVD prevention. By examining the impact of these interventions on modifying lifestyle patterns and improving cardiovascular risk profiles, this trial intends to contribute valuable evidence to guide future preventive strategies and enhance population health outcomes.

## Objectives

We will evaluate whether the use of innovative technologies to gather information on lifestyle and genetic determinants in the primary prevention setting can lead to changes in individuals' behaviors and CVD risk. The primary objective is to assess the efficacy of providing CVD polygenic risk score (CVD PRS) information, measured at baseline, either alone or in combination with the use of an app and a smart band (digital technology), on two endpoints: (i) changes in lifestyle patterns, and (ii) modification in CVD risk profiles. The potential lifestyle modification will also be evaluated in relation to other factors such as psychological status, knowledge and attitudes toward CVDs and personalized medicine, and acceptance of wearable devices, which can influence citizens' behavior.

### Hypothesis

The hypothesis is that achieving the endpoints is more likely with at least one of these interventions (CVD PRS alone or in combination with digital technology) compared to individuals who only undergo the traditional CVD risk assessment at the beginning of the study, as well as compared to individuals who receive traditional risk assessment along with the use of smart band.

## Methods and design

This study protocol was written according to SPIRIT (Standard Protocol Items: Recommendations for Interventional Trials), a guideline that defines standard protocol items for clinical trials and is widely endorsed as an international standard for trial protocols (10, 11).

## Study design

This is an RCT with four parallel arms, as illustrated in Figure 1. Participants will be randomly assigned to the following intervention groups:

A. No Intervention—Traditional CVD risk assessment.B. Traditional CVD risk assessment plus Genetic testing (CVD PRS).C. Traditional CVD risk assessment plus Digital intervention (use of an app and a smart band).D. Traditional CVD risk assessment plus Digital intervention (use of an app and a smart band) plus genetic testing (CVD PRS).

**Figure 1 F1:**
[figure not shown]
The INNOPREV trial.

A detailed explanation of each of the interventions can be found in the “Interventions” section.

## Participants, study setting and recruitment

### Participants, inclusion and exclusion criteria

The study will include individuals between the ages of 40 and 69 years who do not have established CVDs, diabetes mellitus, or familial hypercholesterolemia. These individuals should have a high 10-year CVD risk ranging from 2.5 to 10% based on the SCORE 2 charts (12).

### Study setting

The trial will take place in three regions of Italy: Catania and Palermo (Southern Italy) and Rome (Central Italy). The enrollment of individuals at high cardiovascular risk will occur in different settings per site: primary care ambulatories (Rome), general practitioners' offices (Catania), and a seasonal vaccination center (Palermo).

### Recruitment

The recruitment process will span a period of 8 months, and participants will be followed for a total of 12 months. During the initial medical visit, the physician will inquire about the person's interest in participating in the study. If the person agrees, they will be enrolled, and the planned interventions will be implemented. To ensure effective recruitment, the study will employ a comprehensive advertising campaign targeting the population. This campaign will utilize traditional marketing strategies, including billboards, flyers, and brochures, while also leveraging digital platforms with targeted ads on social networks. These efforts aim to reach and engage a diverse range of potential participants.

## Interventions

All participants will undergo a standardized in-person consultation to receive medical advice for CVD prevention. The advice will be provided in written form and will follow the European Guidelines on cardiovascular risk prevention (14).

### Digital intervention

Participants in groups C and D will be provided with smart bands equipped with sensors to monitor their daily physical activity levels, calories burned, sleep patterns, and heart rate. The collected data will be accessible to the participants through a related mobile app (15) where they can view trends in heart rate, the number of steps taken, daily calorie burn, and the quality of night-time sleep. The app will provide personalized feedback and insights based on the recorded information, such as reminders to achieve a certain number of steps each day to maintain an active lifestyle, in order to reach the optimal suggested number of 6,000–8,000 steps per day (16).

### Genetic testing

Participants assigned to the groups B and D will undergo genetic testing to evaluate their CVD genetic risk profile using a commercially available genome-wide PRS. At the time of enrollment, participants will receive a salivary swab to obtain genomic DNA for analysis. The PRS analysis will be conducted using the Illumina microarray technology, which is a cost-effective genotyping approach for disease and population genetics studies (17). Microarray analysis will generate data on millions of genetic variants per individual, and any gaps between these variants will be filled using imputation analysis. The imputation process compares the sequencing results with a reference dataset, leveraging reference genomes from the 1,000 Genomes Project (18). A modified version of the GLIMPSE algorithm will be utilized for imputing genomic data (19). Based on the combined results, individuals will be classified into three main genetic risk categories for CVD: High risk, Intermediate risk, and Normal risk.

## Study procedure

Eligible individuals accessing primary care ambulatories, general practitioners' offices, and vaccination centers will be invited to participate in the study. They will receive detailed information both orally and through an informative sheet.

Upon enrollment (T0), participants will sign the informed consent form administered by the physicians and will be randomized to one of the four intervention groups through the REDCap (Research Electronic Data Capture) system (19), which will also record all participants information during the study. Participants, research staff, and physicians will be aware of the study group assignment after randomization.

At T0, all participants will undergo a comprehensive assessment and cardiovascular evaluation. This will involve completing questionnaires covering various aspects such as socioeconomic status, area of residence, and key lifestyle factors including smoking, alcohol consumption, dietary patterns, sleep patterns, and physical activity. The lifestyle assessment utilizes the Life's Essential 8 questionnaire, categorizing each participant into a favorable, intermediate, or unfavorable individual lifestyle pattern (20). This metric was recently introduced by the American Heart Association (AHA) for evaluating cardiovascular wellbeing throughout elements such as physical activity, body mass index, and blood pressure, diet, nicotine exposure, blood lipids and blood glucose, and sleep habits (20). The domain of diet has been explored by a new method for the evaluation of individual diet quality as a modified Mediterranean Eating Pattern for Americans (MEPA). This approach emphasizes individuals' dietary patterns and whole food consumption over specific nutrients, promoting its application in clinical and research contexts.

Additionally, participants will be asked questions focusing on psychological status, as well as their knowledge and attitudes toward CVDs, their knowledge and awareness of personalized medicine, genetic testing and PRS, and their acceptance of wearable devices (21–23). All questionnaires are provided in Appendix 1.

The cardiovascular evaluation will include measurements of blood pressure, heart rate, objective examination and cardiovascular risk assessment using SCORE 2 charts, incorporating essential variables such as age, gender, systolic blood pressure, total cholesterol, HDL cholesterol, and smoking status (12). Blood analysis will also be conducted, assessing parameters such as total cholesterol, HDL and LDL cholesterol, triglycerides, high sensitivity C-Reactive Protein (CRP), glycated hemoglobin, and/or glycemia.

Participants in Groups B and D will also undergo a salivary swab for PRS analysis.

Subsequently, participants will have a disclosure visit (T1) after 1 month, a follow-up visit (T2) after 5 months, and a final follow-up visit (T3) at 12 months.

During the disclosure visit (T1), participants in all groups will receive an explanation of their lifestyle pattern and cardiovascular risk profile based on SCORE 2 charts, along with written preventive advice for risk reduction and lifestyle changes. Participants in the digital intervention groups (C, D) will also receive an app and a smart band to monitor various health data. A comprehensive demonstration during smart band delivery, along with written instructions on its usage, will be provided to ensure participants consistently utilize the smart band throughout the study, with the recommendation for daily application (24–26). Participants in the PRS groups (B, D) will receive the disclosure of their genetic CVD risk profile.

At both follow-up visits (T2, T3), the comprehensive questionnaire will be administered again to assess changes in lifestyles and psychological status. Any challenges with smart band usage will also be identified. At the final visit (T3), the cardiovascular risk profile will be recalculated, and participants will undergo a final full assessment, evaluation of the lifestyle category, and blood test to evaluate changes in cholesterol levels and other parameters.

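### As narrated, arm assignment is known at T0 before the self-reported baseline is collected, and nothing requires the baseline to be completed first

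*Protocol article*

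**What the plan says.** All references are to the Protocol article.

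- **Invitation (Study procedure).** "Eligible individuals accessing primary care ambulatories, general practitioners' offices, and vaccination centers will be invited to participate in the study".
- **Consent and allocation (Study procedure).** After signing consent upon enrolment at T0, participants "will be randomized to one of the four intervention groups through the REDCap (Research Electronic Data Capture) system".
- **Unmasking (Study procedure).** "Participants, research staff, and physicians will be aware of the study group assignment after randomization". Randomization and masking says the same, and adds that the allocation table is not disclosed and that the arm becomes known only once randomisation is done.
- **Baseline (Study procedure, next paragraph).** "At T0, all participants will undergo a comprehensive assessment and cardiovascular evaluation". This covers the lifestyle questionnaires, Life's Essential 8, psychological status, knowledge and attitudes, blood pressure, SCORE 2 and bloods.
- **Arm-specific step at T0 (Study procedure).** "Participants in Groups B and D will also undergo a salivary swab for PRS analysis".
- **Eligibility (Participants, inclusion and exclusion criteria).** "These individuals should have a high 10-year CVD risk ranging from 2.5 to 10% based on the SCORE 2 charts". The only baseline SCORE 2 described is the T0 "cardiovascular risk assessment using SCORE 2 charts".
- **Use of the baseline.** The primary outcome is change in lifestyle category from T0 (Outcome measures, Lifestyle change). Baseline psychological status, attitudes to digital technologies and CVD knowledge are planned subgroup factors (Subgroup analyses).

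**The concern.** In an open-label trial the baseline is protected only if it is recorded before anyone in the room knows the arm. The article narrates T0 the other way round and states no safeguard.

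Someone just told that they will, or will not, receive a smart band or a genetic test may report diet, activity, sleep or smoking differently, or answer differently on mood and on attitudes to technology. Two things are then at stake:

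- **Change from baseline.** An arm-related shift in the T0 category passes straight into the primary outcome. Adjusting for a baseline that allocation has already influenced does not remove it.
- **Moderators.** A factor recorded after known allocation is no longer a clean pre-randomisation variable, so an apparent interaction may partly reflect reaction to the assignment.

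The direction cannot be predicted. Under-reporting of healthy habits at T0 in an intervention arm would inflate apparent improvement, and over-reporting would hide it.

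**Working it through.** **1. Order of the T0 steps.** Study procedure gives eligible people invited, consent, randomisation in REDCap, arm known to all, T0 assessment, and swab for B and D. The swab shows that the arm must be known at some point within T0. No sentence puts the questionnaires before allocation, and none says in words that they come after it. The article's only narrated order is allocation first.

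**2. What is exposed.** Of the eight Life's Essential 8 components, four rest on report (diet, physical activity, nicotine exposure, sleep). Four are taken here as measured (body mass index, blood pressure, lipids, glucose). The Discussion says the diet tool is self-administered, open to inaccurate answers and not validated in Italy. The endpoint is a category, so movement in the reported half can carry a person across a boundary.

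**3. The plan's own figure.** Inputs from Sample size estimation: transition rates 15% (D), 10% (C), 8% (B), 5% (A); alpha 0.05; power 80%; withdrawal 30%; 255 per group. The article names no test. For a four-group chi-square with 3 df:

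- mean rate = (0.15 + 0.10 + 0.08 + 0.05)/4 = 0.095
- effect per participant per arm = Σ(p − 0.095)²/(0.095 × 0.905) = 0.0053/0.085975 = 0.0616
- smallest n with power of at least 80% = 177 per group; 177/0.70 = 253, close to the stated 255

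A two-sided D versus A test gives 141 per group, or 202 after withdrawal, which does not match.

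**4. Illustration of size.** The documents give no figure for a reporting shift, so the shifts below are assumptions. Evaluable per arm: 255 × 0.70 = 178.5, taken as 178. For D versus A, two-sided 0.05, the probability of a result favouring D is

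Φ{[(p₁ − p₂) − 1.96√(2p̄(1−p̄)/n)] / √[(p₁(1−p₁) + p₂(1−p₂))/n]}

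Worked case with no shift, 15% versus 5%: (0.10 − 1.96 × 0.0318)/0.03136 = 1.20, so power is about 89%.

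| Assumed shift in D | People (of 178) | True 5% in both, shift inflates D: chance of favouring D | True 15% v 5%, shift masks D: power |
|---|---|---|---|
| 0 points | 0 | 2.5% (nominal) | 89% |
| 1 point | 1.8 | 6% | 83% |
| 2 points | 3.6 | 12% | 75% |
| 3 points | 5.3 | 21% | 66% |
| 5 points | 8.9 | 43% | 43% |

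The planned differences from A are 3 points (B), 5 points (C) and 10 points (D). A 3-point shift would equal the whole planned B versus A difference.

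**5. Eligibility.** Entry needs SCORE 2 between 2.5% and 10%. Study procedure calls invitees eligible before consent, yet the only baseline SCORE 2 and cholesterol described belong to the T0 evaluation. The article does not say which SCORE 2 establishes eligibility.

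**The case against.** **The order is inferred.** Consent, randomisation and assessment are all placed at T0 with no word fixing their order, and text order within the visit is a weak guide. SCORE 2, which needs cholesterol, is narrated before the blood analysis, and the swab, the only arm-specific step, comes last. This stands: the article does not establish that baseline follows allocation. It does mean that a site following the text as written could work in that order.

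**Within-visit order is detail for the full protocol.** Silence alone would be no finding. Here the article does narrate a sequence, and it is the unfavourable one. If the full protocol already puts baseline first, one sentence settles the matter.

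**The exposure is limited.** Bands, app and genetic results arrive at T1, so only knowledge of the arm differs at T0. Half of Life's Essential 8, the lipid outcome and most SCORE 2 inputs are measured. This stands and narrows the concern to the reported components and the questionnaire-based moderators.

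**A stronger reading.** A reader might infer that entry itself is open to allocation-driven bias, or that people found ineligible after allocation would be dropped and break the intention-to-treat set. The documents do not support this. Allocation is concealed (Randomization and masking), invitees are described as already eligible (Study procedure), and all randomised participants are analysed in their allocated arm (Statistical methods for primary and secondary outcomes).

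**Conclusion.** The point holds for the self-reported baseline. The plan neither requires nor states that T0 questionnaires are completed before the arm is known, and its narrative suggests the reverse. The primary outcome's reference category and the questionnaire-based moderators are therefore open to an avoidable bias of unknown size and direction.

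The figures in the table show sensitivity only. They assume 178 evaluable per arm, a simple D versus A comparison and invented shifts, whereas the planned analysis is an adjusted mixed model.

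On eligibility, what remains is an unreconciled description of which SCORE 2 decides entry, not a bias in who enters.

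**What to change.** **Sequence.** State in Study procedure that the T0 questionnaires and on-site measurements (blood pressure, body mass index) are completed and locked in REDCap, and the T0 blood drawn, before REDCap releases the allocation. The saliva swab for B and D follows at the same visit. T0 laboratory results need not be back, because the lifestyle category can be derived later from locked answers. If recruitment has begun, record the order each site has used.

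**Eligibility.** Reconcile the inclusion criteria with the two descriptions in Study procedure (invitees already eligible; SCORE 2 calculated at T0) by saying which SCORE 2 establishes eligibility and when it is obtained.

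**Cost.** A form-order lock in REDCap, a sentence or two of text, and a slightly longer step before allocation. Sample size and analysis are unchanged.

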## Outcome measures

### Primary outcomes

#### Lifestyle change

The Life's Essential eight questionnaire (20) will be administered at T0, T2, and T3 to assess changes in lifestyle category (favorable, intermediate, or unfavorable) compared to baseline.

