### Secondary outcomes

#### Cardiovascular risk change

The SCORE 2 charts will be used to calculate cardiovascular risk at T0, T2, and T3, allowing for the evaluation of changes in risk compared to baseline.

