#### Lipid profile

Blood analysis will be conducted at T0 and T3 to measure changes in lipid levels compared to baseline. Parameters examined will include total cholesterol, HDL and LDL cholesterol, and triglycerides.

By assessing these measures at different time points throughout the trial, the study will evaluate the impact and progress achieved by participants over the course of the intervention.

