## Discussion

This study investigates the efficacy of providing CVD PRS information, alone or in combination with an app and a smart band, on changes in lifestyle patterns and modification of CVD risk profiles.

The aim is to determine whether citizens are more inclined to modify their lifestyle if they are aware of their cardiovascular genetic risk profile and are monitored by an app and smart band that display their levels of physical activity and related parameters.

To date, limited research has explored this aspect, making the INNOPREV trial one of the largest studies in this field.

Previous studies have shown that the provision of personalized genetic information can positively influence screening behaviors and medication adherence for individuals at risk of familial cancers, particularly those with high-penetrance genetic variants (29–31). However, the impact of genetic risk communication on the adoption of complex lifestyle behaviors, such as dietary modification, has not been well-supported by existing evidence (32–37). Systematic reviews investigating the effect of communicating genetic risk on lifestyle modification for cardiometabolic disorders have found no evidence of improved dietary or exercise behaviors (33, 35). Although the studies included in these reviews differ in design characteristics and interventions used, current empirical data consistently suggest that receiving genetic feedback has no significant impact on outcomes, regardless of whether genetic feedback was provided for one gene, multiple genes, or in the form of PRS. Some evidence, however, exists regarding higher initiation of treatments for cholesterol control, such as statins, in groups with genetic information compared to control groups (34, 37).

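### SCORE 2 is planned at T2 without the cholesterol values it needs, and the primary Life's Essential 8 category has the same gap if scored on its listed elements

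*Protocol article*

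**What the plan says.** All references are to the protocol article.

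- **Primary outcome** (Lifestyle change): the Life's Essential 8 questionnaire "will be administered at T0, T2, and T3 to assess changes in lifestyle category (favorable, intermediate, or unfavorable) compared to baseline".
- **Secondary outcome** (Cardiovascular risk change): "The SCORE 2 charts will be used to calculate cardiovascular risk at T0, T2, and T3".
- **Elements of Life's Essential 8** (Study procedure): "physical activity, body mass index, and blood pressure, diet, nicotine exposure, blood lipids and blood glucose, and sleep habits".
- **Inputs to SCORE 2** (Study procedure): "age, gender, systolic blood pressure, total cholesterol, HDL cholesterol, and smoking status".
- **Blood schedule** (Lipid profile): "Blood analysis will be conducted at T0 and T3 to measure changes in lipid levels compared to baseline". The abstract agrees: "Blood samples will be collected at baseline and at study completion to evaluate changes in lipid profiles".
- **What happens at T2** (Study procedure): the questionnaire is repeated and problems with the smart band are noted. No blood test, blood pressure or weight is listed.
- **What happens at T3** (Study procedure): "At the final visit (T3), the cardiovascular risk profile will be recalculated, and participants will undergo a final full assessment". The same sentence also puts the evaluation of the lifestyle category and the blood test at this visit.
- **Analysis** (Statistical methods for primary and secondary outcomes): mixed models compare lifestyle patterns, lipids and CVD risk between baseline and the follow-up visits.

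**The concern.** The outcome section asks for SCORE 2 and the lifestyle category at T2. The procedure section and the blood schedule do not supply what these scores need at that visit. Both schedules are stated in the article, so this is a contradiction and not detail left to a fuller document. No analysis plan can supply a study cholesterol value that was not collected.

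What is at stake is the meaning of the T2 estimates. The models take in T2 along with T3, and the outcome is described as a change from baseline. If T2 is scored from older, self-reported or fewer inputs than T0, part of any apparent change, or of any apparent lack of change, comes from the scoring. This matters more for a three-level category than for a continuous measure, because an altered input can move a participant across a cut-point. The sample size assumes that only 5% (group A) to 15% (group D) of participants move from unfavorable to intermediate. The article gives nothing from which the size of a scoring artefact could be estimated.

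**Working it through.** The plan gives no figure to reproduce here. The check sets the inputs of each score against what is collected at T2.

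**SCORE 2 (6 inputs, Study procedure)**

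| Input | New value at T2? |
|---|---|
| Age | Yes, about 5 months older |
| Gender | Fixed |
| Smoking status | Yes, by questionnaire |
| Systolic blood pressure | Not listed at T2 |
| Total cholesterol | No, blood only at T0 and T3 |
| HDL cholesterol | No, blood only at T0 and T3 |

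- Without a new value for certain: 2 of 6 = 33%.
- If blood pressure is also not taken: 3 of 6 = 50%. Gender is fixed, so only smoking status and 5 months of age could then change the score.

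**Life's Essential 8 (8 elements, Study procedure)**

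| Element | New value at T2? |
|---|---|
| Diet, physical activity, nicotine, sleep (4) | Yes, by questionnaire |
| Body mass index, blood pressure (2) | Not listed at T2 |
| Blood lipids, blood glucose (2) | No, blood only at T0 and T3 |

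- Without a new laboratory value, if the category uses these elements: 2 of 8 = 25%.
- If body mass index and blood pressure are also not taken: 4 of 8 = 50%.

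**Visit by visit**

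- T0: questionnaire, cardiovascular evaluation and bloods. Both scores can be computed.
- T2: questionnaire only, as listed. SCORE 2 lacks its cholesterol inputs. The category lacks at least its two blood elements if it uses them.
- T3: questionnaire, full assessment and bloods. Both scores can be computed.

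The change from T0 to T3 is therefore like for like. The change from T0 to T2 is not for SCORE 2, and is not for the full category if the listed elements are scored. The procedure section agrees with this reading, since it places both the recalculated risk and the lifestyle category at T3. The outcome section is the part that departs from it.

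**The case against.** The strongest reply concerns the primary outcome. The article calls Life's Essential 8 a questionnaire that is administered, and its list of elements describes the published metric. The instrument used is in Appendix 1, which is not shown. If the trial scores the category from questionnaire answers alone, in the same way at every visit, the T2 category can be computed and its change from T0 is valid. This stands, and it makes the primary-outcome part conditional. It does not help SCORE 2, whose inputs the article states outright.

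Second, the article is condensed, and blood pressure or weight may be taken at T2 without being mentioned. This also stands, so 3 of 6 and 4 of 8 are upper counts. The lower counts of 2 of 6 and 2 of 8 rest on the stated blood schedule.

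Third, outside laboratory results or self-reported values could fill the gap. The article does not say so. Set beside study bloods at T0 and T3, they would not be a like-for-like measurement.

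A reader might go further and infer that the T2 values will be frozen baseline data, or that the treatment effect will be halved. The documents do not support either reading. Carry-forward is mentioned nowhere. Halving would need an effect acting wholly through lipids, carry-forward at T2 and equal averaging of T2 with T3, none of which is stated. The analysis section reads more naturally as comparisons at each visit.

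**Conclusion.** The conflict is real and the passages need to be reconciled. For SCORE 2 it is firm: the score cannot be validly recalculated at T2 on the stated blood schedule, with 2 of 6 inputs lacking a new value, or 3 of 6 if blood pressure is not taken. For the primary Life's Essential 8 category it holds on the assumption that the category is scored with the elements listed under Study procedure. In that case 2 of 8 elements lack a new value, or 4 of 8 if body mass index and blood pressure are not taken.

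A reader might infer that the primary outcome as a whole cannot be measured. That is not so. The comparison of T0 with T3 is intact for both outcomes, and diet, physical activity, nicotine and sleep can be assessed at T2. A score with fewer items is also valid, provided the same items are scored in the same way at every visit. The fault is limited to the T2 values as now defined and to their entry into the repeated-measures models.

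**What to change.** Reconcile Study procedure, Outcome measures and Statistical methods as follows.

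1. Limit SCORE 2 to T0 and T3, and analyse T3 with adjustment for T0.
2. Limit the full Life's Essential 8 category to T0 and T3, name T3 as the primary time point, and adjust for T0.
3. At T2 analyse only a behavioural sub-score (diet, physical activity, nicotine, sleep), with the same items and scoring at T0, T2 and T3. The repeated-measures model then applies to this sub-score.
4. State which elements enter the lifestyle category. If Appendix 1 already scores it from questionnaire items alone, say so and correct the description under Study procedure. Step 1 is needed in either case.

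The cost is wording. No visit, blood draw or participant is added. The downside is that there is no mid-trial estimate of SCORE 2 or of the full category, which the stated blood schedule cannot support. Measuring the missing components at T2 would also resolve the conflict, but it adds a blood draw and, if not already done, blood pressure and body mass index measurements for every participant attending that visit.
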